### Exploratory analysis of EED biomarkers in fecal samples

Stool samples will be collected using plastic-lined diapers and aliquots of stool transferred using sterile metal spatulas into cryovials and flash frozen in liquid nitrogen within five minutes of defecation. Novel fecal biomarkers will be sought to assess bowel integrity and levels of inflammation noninvasively. Evaluation of these markers of barrier dysfunction might pave the way for assessment of intestinal mucosal permeability and inflammatory response in diagnosing the degree and progression of EED in vulnerable populations without the need for the relatively lengthy and cumbersome dual-sugar absorption test [53–61]. Markers of interest include cytokines, interleukins, immunoglobulins, REG1A, REG1B, calprotectin, and zonulin.

We also plan to continue our exploration of human mRNA transcripts of putative inflammatory and antimicrobial mediators that are upregulated in EED and found in fecal samples. Nucleic acids are first extracted using a NucliSens EasyMAG kit (BioMérieux), which is a bead-based RNA-specific method. A digital droplet PCR is used to detect low copy numbers of human mRNA reliably [62]. The digital droplet PCR is unique in that after the PCR is set up in the aqueous phase, the reaction is emulsified in oil, creating 20,000 aqueous bubbles that are counted by laser for positive fluorescence of the probe of interest. The quantities of mRNA in a given sample are normalized to a housekeeping gene present in abundant quantities. A number of promising targets that correlate with EED have already been identified (unpublished data) and these will be pursued further in this study, with the aim of identifying one or more that may serve as less cumbersome biomarkers of EED. Newer whole human transcriptome microarray technology [63, 64] will also be employed to interrogate these samples, as another approach to identify these biomarkers.

### Microbiome analysis

To investigate correlations between bacterial populations in the gut and EED, as well as the effects of the legume interventions on gut microbe populations, bacterial genomic DNA will be prepared separately from fecal samples obtained from study children. To prepare the stool samples for sequencing, genomic DNA will be extracted using standard protocols (http://hmpdacc.org/resources/tools_protocols.php) V1-V3 variable regions of bacterial 16S rRNA genes will be amplified by PCR and the resulting amplicons will be subjected to high throughput sequencing. We will use the to Illumina Miseq platform for targeted 16S rRNA sequencing. This deep sequencing permits the recognition of rare members of the microbiota that may be shared or that may discriminate these human populations. 16S rRNA sequences will be processed through the pipeline developed by human microbiome projects at The Genome Institute at Washington University. In brief, quality trimming, denosing and chimera removal will be performed to yield high quality reads [65]. Reads passing the above filtering steps will be classified from the phylum to the genus level using an automated implementation of the Ribosomal Database Project’s Classifier [66]. Species-level bacterial phylotypes will be defined as organisms sharing at least 97 % nucleotide sequence identity in the V1-V3 regions of their 16S rRNA genes using the Mothur software package [67].

Shotgun sequencing will be performed to examine the taxa that are prominently represented in the infant microbiome but inefficiently captured by PCR primers designed to target other variable regions. Whole genome sequencing libraries will be prepared following a standard protocol from Illumina. Ten GB 100 bp pair-end reads per sample will be sequenced on the Illumina HiSeq platform. Reads passing quality filtering and human contamination removal will be classified to species level based on nucleotide sequence alignment to reference genomes using Real Time Genomics map software (Real Time Genomics, San Bruno, CA, USA). Read mapping results will be transformed to values representing the coverage of each reference genome using refcov software (http://gmt.genome.wustl.edu/packages/refcov/index.html). The coverage values are then scaled to a million aligned reads to calculate ‘depth of coverage per million reads’ values. Taxa-based analysis will be the same as the 16S rRNA genes approach described above.

### Data management and analysis

Clinical data such as anthropometry, demography, and morbidity data, will be collected on standardized forms by field workers. Field workers will be trained and validated with the questionnaires and measurements they collect prior to data collection. Anthropometric Z-scores will be calculated from the 2006 WHO Multicentre Growth Reference Survey [68]. Data will be double-entered into a password-protected Microsoft Access database by research assistants blinded to food assignments. All discrepancies will be resolved by examination of the original data cards and discussion with the relevant field workers, possibly including repeat examination of the child and questioning of the caregiver as needed. Once all values are entered and discrepancies resolved, the data set will be locked.

Comparisons will be made between cowpea flour and corn–soy blended flour, separately from common beans and corn–soy blend. Fisher’s exact test will generally be used to compare discrete parameters, and Student’s *t* test will be used for continuous parameters. A difference with *P* < 0.05 will be considered statistically significant. These statistical methods will also be used for all clinical data and EED measures (*e.g.*, L:M ratio), which are continuous measures of EED status.

The microbiome data analyses and interpretation require specialized tools. Read-based metabolic profiling of the microbial communities is performed by first using whole genome sequencing reads from each sample to probe the *Kyoto Encyclopedia of Genes and Genomes* using Mblastx (MultiCoreWare, St. Louis, MO) and then search results are run through the metabolic pathway pipeline developed as part of the Human Microbiome Project to obtain enzyme and pathway abundance and coverage from metagenomic communities. Differentially expressed enzymes and pathways between groups (both between intervention groups as well as within the same individual, for example before and after intervention) are identified using LEfSe (http://huttenhower.sph.harvard.edu/lefse). Principal component analysis will be performed to identify cluster patterns based on the gene content and metabolic pathway abundance between the legume and corn–soy blend groups.

All microbiome data will be rarefied to ensure the sample comparisons are at the same read depth. Ordination methods will facilitate the pattern analysis of the high dimensional microbiome data by reducing its dimensionality to 2–3 dimensions, such that the original distance between the samples is preserved to a large degree. In particular, principal component analysis with Bray–Curtis dissimilarity will be used to identify the sample cluster pattern based on the microbial community structures.

A robust statistical approach that is widely used in ecology and metagenomics, Permutational Multivariate Analysis of Variance (perMANOVA in the R software package, http://www.r-project.org), will be used to test the significance of differences at the whole bacterial community level between two or more groups. Dissimilarity matrices will be generated based on the taxon abundance table, and will be treated as the dependent variable in the model. We will use metastats, a program developed in the Human Microbiome Project, to detect differentially abundant taxa between groups [69]. The statistical tests will be corrected for false discovery rates using the q-values approach, an approach that has been effectively applied in metagenomic studies for identifying the taxa of interest. Indices such as richness (the total different number of taxa) and Shannon diversity (the number of taxa present as well as the relative abundances) that categorize the complexity of the bacteria community will be computed. Student’s t-test will be used to compare the diversity differences between groups.

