### Primary outcome measures and sample size

The primary outcome measures of interest will be change in height-for-age Z score and improvement in the major biomarker of environmental enteropathy, the lactulose to mannitol ratio (L:M) [34]. To detect a difference in change in length of 1.1 cm, which corresponds to a change in height-for-age Z score of 0.45 units at 12 months of age, 79 children are needed in each group. This sample size was calculated for a two-tailed test using G*Power 3.1.9.2 [35] at a significance level of 0.05 and 80 % power.

We also desire to detect a (medium) effect size of 0.5 in the L:M test after the legume intervention, again with 80 % power at a significance level of 0.05. Given these parameters, if the L:M results were to follow a normal distribution, thereby allowing the use of Student’s *t* test to compare the differences between independent means, 64 children would be needed in each group. If the L:M results are not normally distributed and require nonparametric analysis with the Wilcoxon–Mann–Whitney test, then up to 74 children might be needed per group. In recent studies, we have experienced approximately a 5 % rate of insufficient urine specimens [8]. We therefore very conservatively estimate that this rate might increase to 15–20 %. Thus, we believe that enrolling 300 children with a 15–20 % rate of failure to obtain sufficient urine (owing to dropouts and specimen collection failures) will yield complete analysis for at least 240 children, or 80 in each group.

Should 100 children indeed be enrolled and retained in each intervention arm, the power achieved for the height-for-age Z score criterion is 89 % and for the L:M criteria is 94 % (if normally distributed) and 93 % (if non-normally distributied).

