### Dual-sugar absorption test

The dual-sugar permeability test [34] will be used as a standard noninvasive measure of gut integrity, as it correlates with the severity of small bowel histological changes [46], severity of diarrhea [47], micronutrient status [48, 49], and growth in weight and length [50]. The ratio of urinary excretion of lactulose to mannitol is used to measure intestinal mucosal permeability with higher ratios indicative of increased intestinal permeability.

To participate in the test, children will be asked to take no food (water and breast milk are permitted) after 10 p.m. on the previous night. The test begins when each child drinks a 20 ml solution containing 1 g mannitol and 5 g lactulose. Children will be carefully observed by research assistants to ensure complete ingestion of this solution; any child who spits up, vomits, or refuses the solution will be brought back for testing on another day. Adhesive urine bags will then be placed on the child’s perineum and monitored for urine output. As soon as urine is noted in the bag, it will be removed and the urine transferred to a clean container containing 10 mg merthiolate to prevent bacterial degradation of the excreted sugars, and a new bag will be placed. After 3–3.5 hours, children will be given water to drink to facilitate the collection of urine. After the child voids for the first time after 4 hours, the urine collection will be omplete. The total amount of urine voided during the study will then be quantified and an aliquot flash frozen for analysis.

The concentrations of lactulose and mannitol in the total voided urine will be determined using HPLC, as described previously [51]. Given a recent report that HPLC is less reliable than liquid chromatography-tandem mass spectrometry [52], we previously compared our L:M results by HPLC on 115 samples with those obtained by the Mayo Clinic performed using liquid chromatography-tandem mass spectrometry and we found the results to be highly correlated (data not shown). The concentrations of these sugars in the urine will then be multiplied by the total amount of urine voided to provide a measure of the total amount of these sugars voided. The ratio of the sugars voided in the urine, as well as the amount voided as a percentage of the amount ingested, will be computed and compared between groups.

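### The primary L:M test is fixed as Student's t in the analysis section but made conditional on normality in the sizing section, so neither the test nor the quantity it estimates is settled

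*Protocol article*

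**What the plan says.** Under Primary outcome measures and sample size, the article makes change in height-for-age Z score and improvement in L:M the primary outcomes. For L:M it targets a standardised effect of 0.5, "again with 80 % power at a significance level of 0.05". It then gives two sizes. With normal data and Student's t test, "64 children would be needed in each group". The alternative begins "If the L:M results are not normally distributed and require nonparametric analysis" and leads to Wilcoxon–Mann–Whitney with up to 74 per group. Planned evaluable numbers are 80 per arm. For 100 per arm it quotes power of 94 % (normal) and 93 % (non-normal).

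Under Data management and analysis, each legume is compared separately with corn–soy blend, by Fisher's exact test for discrete and Student's t test for continuous parameters, at P < 0.05. The next sentence extends this: "These statistical methods will also be used for all clinical data and EED measures", with L:M as the example. That section mentions no normality condition, transformation or rank test for clinical or EED measures.

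**The concern.** The sizing section makes the L:M test conditional on the distribution; the analysis section makes it unconditional. With non-normal results, one points to Wilcoxon and the other to t. A reader could not tell which P value is the primary result.

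The conditional rule has its own weakness. It says nothing about how normality is judged, on which data, or by whom, so the choice could follow sight of the outcome. The tests also answer different questions: t compares mean L:M, Wilcoxon compares ranks. The estimated quantity would therefore depend on the data too.

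Scale matters because L:M is a positive ratio of two excreted amounts. Such a ratio can be right-skewed, and a few high values then weigh heavily on the mean and its variance. The article does not say whether 0.5 is in SD units of raw or of log L:M.

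**Working it through.** **Inputs from the article (sizing section):** d = 0.5, α = 0.05, power 80 %, 64 or up to 74 per group, 80 evaluable per arm, 94 % and 93 % power at 100 per arm. Two-sided testing is stated for the height-for-age calculation and taken to apply here.

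**Assumptions of this check:** lognormal L:M with log-SD s from 0.4 to 1.1. The article gives no L:M distribution, so a range is shown.

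**1. The plan's own figures.** For the t test, power is P(T′ > t₀.₉₇₅) with 2n − 2 degrees of freedom and noncentrality δ = d√(n/2).
- Solving for 80 % power gives n = 63.8, so 64. At n = 64, δ = 0.5√32 = 2.83 and power is 80.1 %.
- Wilcoxon at its minimum asymptotic relative efficiency, 0.864: 63.8/0.864 = 73.8, so 74.
- At 100 per arm, δ = 0.5√50 = 3.54 and t has 94.0 %. Wilcoxon has 93.0 % with the normal-parent efficiency 3/π = 0.955, or 90.5 % with the 0.864 behind the 74.
- At 80 per arm, t has 88.2 % and Wilcoxon at minimum efficiency 83.1 %.

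All the stated L:M figures reproduce, the 93 % only with the normal-parent efficiency.

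**2. Effect of 0.5 in raw SD units.** The raw SD of exp(sZ), with Z standard normal, is √[(e^{s²} − 1)e^{s²}]. Shift one arm by half of that. Simulated power at 80 per arm is 87–89 % for t on raw L:M at every s examined, matching the 88.2 % of normal theory. Wilcoxon reaches 95–100 % for s from 0.4 to 1.0. Skewness makes t the less efficient test here but does not take it below the planned power.

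**3. Effect of 0.5 in log-SD units.** Multiply one arm by exp(−0.5s). Simulated power at 80 per arm:

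| log-SD | t on raw L:M | Wilcoxon | t on log L:M |
|---|---|---|---|
| 0.5 | about 83 % | about 87 % | about 88 % |
| 0.7 | about 80 % | about 87 % | about 88 % |
| 0.9 | about 75 % | about 87 % | about 88 % |
| 1.1 | about 67 % | about 87 % | about 88 % |

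Repeat simulations agree within about one percentage point. On this reading raw t reaches the 80 % target at a log-SD of about 0.7 and falls below it beyond that.

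**4. Does the choice of test change the answer?** Same lognormal assumption, 80 per arm.
- No true effect: t and Wilcoxon disagree on significance in 4–6 % of trials. If either could be reported, the false-positive rate would be about 7–8 % instead of 5 %. That is an upper bound for an open choice, not the error rate of a fixed normality rule.
- True shift of 0.5 log-SD: they disagree in about 8 %, 12 %, 19 % and 24 % of trials at log-SD 0.5, 0.7, 0.9 and 1.1.

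**The case against.** The strongest reply is that the conflict is partial and the trial is large enough either way. Student's t is one of the two tests the sizing section allows, that paragraph's purpose is to count children, and 80 per arm exceeds both 64 and 74. The t test is also valid for a difference in means at this size: simulated type I error under lognormal data was 4–5 %. Transformation, covariates and sensitivity analyses are commonly left to an analysis plan that is not shown. All of this stands, and it means that the absence of a log transformation is not in itself a fault. It does not remove the conflict, because the article names a test for L:M in one section and a different rule in another.

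A reader might go further and infer that a t test on raw L:M loses the stated power. The documents do not support that in general. They do not say that L:M is skewed, and with 0.5 in raw SD units the power is kept. Nor does the article expect non-normality; it provides for both cases with an if.

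A reader might also infer a much larger loss by setting raw change scores against a baseline-adjusted log analysis. That comparison mixes scale, change scoring and baseline adjustment, and needs a baseline-to-final correlation that the article does not give.

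**Conclusion.** The point holds as an inconsistency in a primary analysis. The two sections give different tests for L:M whenever it is judged non-normal, no criterion decides that, and the scale of the effect size is not stated. The test and its estimand are therefore not uniquely fixed.

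The sample size is not in error. Any loss of power against the plan is conditional on two things the article does not state: an effect of 0.5 in log-SD units and right-skewed L:M. If both hold, raw t at 80 evaluable per arm has about 83 % to 67 % over log-SD 0.5 to 1.1. If 0.5 is in raw SD units, it has about 88 %. On skewed data raw t is less efficient than Wilcoxon under either reading, which is a reason to settle the scale in advance.

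**What to change.** In Data management and analysis, and before unblinding, name one primary L:M analysis on one scale. One suitable choice among several is natural-log L:M at the final visit (week 24 in Study 1, week 48 in Study 2), each legume arm against corn–soy blend, by linear regression on log baseline L:M, reported as a geometric mean ratio with 95 % CI. Name Wilcoxon–Mann–Whitney as a sensitivity analysis. In Primary outcome measures and sample size, reword the normal/non-normal passage so that the test does not depend on the observed distribution, and state the scale of the 0.5 effect size.

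The cost is wording only: the visit schedules already include the dual-sugar test at week 0 and at both final visits. The result becomes a ratio of geometric means rather than a difference in means. Baseline adjustment should also help modestly. With an assumed baseline-to-final correlation of 0.3 on the log scale, the effective standardised effect is 0.5/√(1 − 0.3²) = 0.524, and power at 80 per arm is about 91 %, against 88 % for unadjusted log t.

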### Study participation

After obtaining verbal and written consent from caregivers of eligible children, randomization will occur and basic sociodemographic, food frequency, and economic data will be collected. Recent illnesses during the previous 7 days will be queried at each visit [43]. At the initial visit, anthropometric data will be gathered to ensure that the child is not acutely malnourished and thus ineligible for the study. If eligible, the child will continue with the dual-sugar absorption test and stool collection. After successful completion of the dual-sugar absorption test and stool collection, a 6-week supply of the assigned flour intervention will be provided and the caregiver will be educated on how to prepare and feed the flour to the child. The complete schedule of study visits, testing, and distribution of flours is provided in Table 3 for Study 1 and Table 4 for Study 2.

**Table 3 Tab3:** Study participation schedule for subjects enrolled in Study 1

	Anthropometry	Dual-sugar absorption test	Stool collection for EED biomarker and microbiome studies	Intervention flour distribution
Week 0	X	X	X	X
Week 2	X		X	
Week 6	X		X	X
Week 12	X	X	X	X
Week 18	X		X	X
Week 24	X	X	X

**Table 4 Tab4:** Study participation schedule for subjects enrolled in Study 2

	Anthropometry	Dual-sugar absorption test	Stool collection for EED biomarker and microbiome studies	Intervention flour distribution
Week 0	X	X	X	X
Week 2	X		X	
Week 6	X		X	X
Week 12	X	X	X	X
Week 18	X			X
Week 24	X	X	X	X
Week 30	X			X
Week 36	X	X	X	X
Week 42	X			X
Week 48	X	X	X	

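### LEfSe, an independent-samples method, is assigned to before/after comparisons within the same child, which discards the pairing and costs power; the Bray–Curtis ordination is misnamed

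*Protocol article*

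**What the plan says.** The statements are in the Protocol article, Data management and analysis, unless noted.

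- **Enzymes and pathways.** Features that differ between groups "are identified using LEfSe". The groups are defined in a parenthesis as "both between intervention groups as well as within the same individual, for example before and after intervention". No paired test, subject blocking or random effect is named for the second kind of comparison.
- **Taxa.** perMANOVA "will be used to test the significance of differences at the whole bacterial community level between two or more groups". Metastats is used "to detect differentially abundant taxa between groups". Diversity indices are compared between groups by Student's t test. False discovery is controlled with q-values.
- **Ordination of taxa.** The text names "principal component analysis with Bray–Curtis dissimilarity will be used to identify the sample cluster pattern based on the microbial community structures".
- **Ordination of genes and pathways.** "Principal component analysis will be performed to identify cluster patterns based on the gene content and metabolic pathway abundance"; no dissimilarity is attached to this one.
- **Repeated sampling (Study participation, Tables 3 and 4).** The column "Stool collection for EED biomarker and microbiome studies" is marked at weeks 0, 2, 6, 12, 18 and 24 in Study 1 (6 stools) and at weeks 0, 2, 6, 12, 24, 36 and 48 in Study 2 (7 stools).
- **Control (Intervention groups).** Children are randomized 1:1:1 to common bean, cowpea or corn–soy flour.

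**The concern.** A child's stools before and after the intervention share that child's stable characteristics, so they are normally positively correlated. A paired analysis removes the shared part; an independent-samples analysis leaves it in the error term. The plan schedules serial stools and names within-child change as a comparison of interest, then gives it to a tool that cannot use the pairing. Real changes in pathway abundance would be missed more often than necessary.

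A second question is what a before/after result would mean. Study 1 children go from about 6 to 12 months of age while on the flour, and the Background (Microbiome) refers to the maturation of young children's intestinal microbiota. A change within one arm is flour plus ageing.

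Third, principal component analysis works on Euclidean distance, so coupling it with Bray–Curtis does not describe a defined procedure. Two analysts could do different things: PCA on the abundance table, or principal coordinates on the dissimilarity matrix.

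Effects on the intestinal microbiome are a stated aim of both trials, but they are not a primary outcome.

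**Working it through.** The article gives no power or sample size for the microbiome, so there is no stated figure to reproduce. What follows is illustrative and is per feature at a two-sided 5% level, before any q-value correction.

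**Inputs**
- n = 80 children in one arm. This is the article's figure for complete analyses per group (Primary outcome measures and sample size). It was derived for urine samples and is borrowed here only as a plausible size.
- Before/after shift d = 0.3 SD: assumed.
- Within-child correlation r = 0.3, 0.5, 0.7: assumed, because the article gives none.
- LEfSe's screen, with two groups, behaves as an unpaired rank-sum test. This is a property of the tool; the article does not describe it.

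**Step 1: normal approximation**

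True standard error of the mean change: SE = √(2(1 − r)/n).
Standard error that an unpaired test assumes: √(2/80) = 0.1581, so it rejects when the difference exceeds 1.96 × 0.1581 = 0.3099.

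- Type I error, unpaired: 2 × P(Z > 1.96/√(1 − r)). At r = 0.5: 2 × P(Z > 2.77) = 0.6%.
- Power, unpaired: P(Z > (0.3099 − 0.3)/SE). At r = 0.5, SE = 0.1118: P(Z > 0.089) = 46%.
- Power, paired: P(Z < 0.3/SE − 1.96). At r = 0.5: P(Z < 2.683 − 1.96) = 77%.

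**Step 2: simulation with the rank tests themselves** (4,000 replicates, normal data, rank-sum against signed-rank, n = 80)

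| r | Type I, unpaired | Type I, paired | Power, unpaired | Power, paired |
|---|---|---|---|---|
| 0 | 5.2% | 5.4% | 45% | 45% |
| 0.3 | 2.0% | 4.9% | 45% | 60% |
| 0.5 | 0.7% | 5.0% | 45% | 74% |
| 0.7 | 0.1% | 4.9% | 43% | 92% |

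The two steps agree closely. With n = 100 the pattern is the same: 55–57% unpaired against 69%, 83% and 97% paired for r = 0.3, 0.5 and 0.7.

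**Step 3: maturation**

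Now let the 0.3 SD shift be pure ageing, equal in both arms, with no flour effect. A paired within-arm test detects it 60–92% of the time, as in the table. That is correct as a statement about change and wrong if read as a flour effect. Comparing the change between arms on such data rejects in 5.6%, 4.6% and 4.9% of replicates at r = 0.3, 0.5 and 0.7, so it holds its nominal level.

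**Step 4: ordination**

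A Bray–Curtis matrix on simulated counts (40 samples, 60 taxa), squared and double-centred, had 4 negative eigenvalues out of 40, together about 1.4% of the positive total. The dissimilarity is therefore not Euclidean, and PCA cannot represent it as such. Principal coordinates analysis and NMDS both take it as input.

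**The case against.** The best defence is that most of this is exploratory and condensed. The before/after contrast appears only as an example, between-arm comparison is named first, and the primary outcomes (height-for-age Z score and L:M) are untouched. The power figures rest on an assumed shift and assumed correlations, and the article sets no power target for the microbiome. All of this stands and limits the weight of the point. It does not remove it, because the sentence does assign LEfSe to data from the same individual; that is stated text, not a detail left to another document.

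Three stronger readings are tempting and are not supported.

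- **That repeated stools are pooled as independent in perMANOVA, metastats and the t test, inflating false positives.** Treating 6 stools per child as independent with an intraclass correlation of 0.1 would give a design effect of 1 + 5 × 0.1 = 1.5 and an error near 11%. But the article describes these methods only as comparisons between groups. It never says that all visits enter together, nor that every stool is sequenced. Which visit is used is something an article may leave to the full protocol or SAP.
- **That maturation confounds the microbiome results.** It affects any before/after reading, paired or unpaired, so it does not follow from the choice of tool. The randomized comparisons with corn–soy are not confounded by it, and the article does not say that a within-arm change will be taken as the intervention effect.
- **That the ordination cannot be carried out.** The sentence before it speaks of preserving distances between samples in 2–3 dimensions, which is what principal coordinates analysis does. This is most likely a naming slip in a descriptive step that carries no test. The PCA on gene and pathway content is feasible as written.

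**Conclusion.** The point holds in a narrow form. Following the text, the before/after analysis of enzymes and pathways would use an independent-samples method on paired data. With positive within-child correlation the test is conservative (actual error about 2.0%, 0.7% and 0.1% at r = 0.3, 0.5 and 0.7) and loses power: about 45% instead of about 60%, 74% and 92%, given 80 children and a 0.3 SD shift. The direction of the loss depends only on the correlation being positive; its size depends on the assumed values, and at zero correlation there is none. These figures concern detection of change over time in one arm, not the power of a comparison between arms.

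A within-arm change is not by itself evidence for the flour; the concurrent corn–soy arm supplies the contrast that is. The Bray–Curtis wording is a minor correction.

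**What to change.** 1. For before/after enzyme and pathway data, replace LEfSe with a paired or child-blocked method, for example a signed-rank test on within-child change or a mixed model with child as a random effect.
2. State that the intervention effect is the between-arm difference in change (arm by time) for each legume against corn–soy, and that within-arm change is descriptive of time plus flour.
3. State that the q-value correction already planned covers these tests.
4. Keep LEfSe for comparisons between arms at a single visit.
5. Where Bray–Curtis is used, write principal coordinates analysis (or NMDS). Leave the PCA on gene and pathway content as it is.

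The cost is a few sentences and standard software. No samples, visits or sequencing are added, and the primary analyses do not change.
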